### Unblinding after the study

When all trials are completed and all data have been locked, the unblinding process will be conducted in the presence of the researchers.

### Interventions

On the basis of conventional western medicine treatment, the *Guhong* group will be given a 20-ml intravenous infusion of *Guhong* injection that was diluted with 250 ml 0.9% sodium chloride injection once a day, while the control group will be given 270 ml 0.9% sodium chloride injection as placebo treatment once a day. (*Guhong* injection is provided by China tonghua guhong pharmaceutical co. Ltd. The production batch number is 20190306 and each bottle has a capacity of 5 ml. The drug distributed to each center will be labeled with the statement “for trial only” and the information of the name, dosage, dosing plan, indications, storage conditions, expiratory date, manufacturer and so on. Each center has an independent manager responsible for receiving, handling, storing and distributing the medications.) The course of treatment is 10 days. On the day of enrollment and at the end of treatment, the clinical symptoms and signs of angina pectoris will be recorded, the quantitative table of TCM syndrome will be scored, the electrocardiogram (ECG) will be examined, and the indicators of inflammation, endothelial function, myocardial metabolites and related biochemical tests will be conducted. Moreover, patients will be followed up for 8 weeks after the end of treatment, including any improvement in angina pectoris and the TCM syndrome quantitative score. During the entire study period, participants will be visited for a total of four times by the investigators. Specific research process details are provided in Table 2.

**Table 2 Tab2:**
[figure not shown]
Study schedule for patients

### Concomitant treatments and forbidden drugs

During the study period, participants with other diseases, such as hypertension, diabetes, hyperlipidemia, etc., are allowed to continue any corresponding treatment using western medicine. Also the name, dosage and duration of any concomitant medication must be carefully recorded in the CRF, and any other western medicine or Chinese medicine that may affect the research results will be prohibited. Once banned drugs are used, patients will be removed from the study and their data will not be used, in accordance with the signed ICF.

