### Efficacy assessment

#### Primary outcome

The criteria for therapeutic efficiency evaluation is based on the principles for clinical research reports on cardiovascular drugs formulated by the National Health and Pharmaceutical Bureau of China [13] by comparing the anginal attack frequency and ECG changes before and after treatment in the two groups of participants. Specific evaluation criteria are shown in Table 3.

**Table 3 Tab3:** Evaluation criteria on the therapeutic efficiency

Three-graded criteria	Detailed description	Classification
Significant improvement	Anginal attacks disappeared or significantly improved, decreased by 80%; electrocardiogram (ECG) returned to normal or substantially normal	Significantly effective
Improvement	Anginal attacks improved or the frequency of anginal attacks decreased by 50–80%; the descending ST segment of the ECG rose ≥ 0.05 mV, and the ascending ST segment fell ≥ 0.05 mV, but still did not return to normal; or the T wave of the main ECG lead changed from flat to upright; or the T wave changed from inverted to shallow by more than 50%	Effective
No improvement	No change or even aggravation of anginal attacks, no decrease or even increase of the frequency of angina pectoris attacks, no change or even aggravation of ECG ST-T segment	No effect

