#### Data management and statistical analysis

The Drug Clinical Research Center of Guangzhou University of TCM will be responsible for the data statistical analysis. Two independent data administrators are in charge of reading the CRFs and recording data on the EpiData 3.1 software. Clinical research assistants (CRA) and investigators will re-check and review the accuracy and consistency of the data. After entering and reviewing, the database will be locked and the statistical analysis will be performed only with the permission of the sponsor, the principal investigator and the investigators.

The full analysis set (FAS) is the primary analysis set, in which patients should be dosed with *Guhong* injection or placebo for 10 days with clinical observations recorded in the study. All subjects without any major protocol deviations will be included in the per-protocol set (PPS). Efficacy assessment will be performed through FAS and PPS. Safety evaluation will be conducted for those who have been treated at least once, which is defined as the safety set (SS).

All continuous data and normal distribution data are represented by mean ± standard deviation, with median and range for non-normal data. Classified data are expressed in frequency counts and percentages. Baseline balance between groups will be determined by a chi-square test or analysis of covariance (ANOVA). All the indicators of anginal attack frequency, inflammation, endothelial function and myocardial metabolites will be estimated and compared using the log-rank test. A Kaplan-Meier survival curve will be constructed, and the median time will be provided separately for each group with a two-sided 95% confidence interval. ANOVA and Bonferroni methods will be used to compare the TCM symptom and sign scores of the two groups. All collected data will be processed by professional statisticians using SAS 9.2 software; a two-sided *P* value of < 0.05 is considered statistically significant.

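### The rule that discards all data of prohibited-drug users conflicts with the definitions of the safety set and the full analysis set, and can bias the efficacy comparison in either direction

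*Protocol article*

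**What the plan says.** Under 'Concomitant treatments and forbidden drugs', the Protocol article lets patients continue western treatment for other diseases and then states that "any other western medicine or Chinese medicine that may affect the research results will be prohibited". The consequence follows: "Once banned drugs are used, patients will be removed from the study and their data will not be used", which is said to accord with the signed consent form. The ban runs through the study period. Under 'Interventions', that period includes 8 weeks of follow-up after the 10 treatment days.

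'Data management and statistical analysis' defines three sets:

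- Safety set: "Safety evaluation will be conducted for those who have been treated at least once".
- FAS, named as the primary set: patients dosed for 10 days with clinical observations recorded.
- PPS: subjects without major protocol deviations.

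It adds: "Efficacy assessment will be performed through FAS and PPS". Neither the safety set nor the FAS excludes users of prohibited drugs.

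Under 'Primary outcome', efficacy is graded from anginal frequency and ECG before and after treatment. The lowest grade in Table 3 includes "No change or even aggravation of anginal attacks, no decrease or even increase of the frequency of angina pectoris attacks".

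**The concern.** Taking a prohibited drug is an event after randomisation. Removing patients because of such an event means that the groups compared are no longer the groups randomised. The ban is defined by a drug's capacity to influence the results, and the primary outcome is built on angina. A patient whose angina persists has an obvious reason to look for extra treatment, so the exclusion may well depend on outcome. If it does, the effective rate in each arm is overstated, and the difference between arms can move either way, depending on which arm loses more failures.

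Safety is also affected. A patient who received infusions and then took a prohibited drug would leave the safety evaluation together with any adverse event already recorded. Safety is one of the trial's stated aims, and one of its stopping guidelines rests on intolerable adverse reactions.

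**Working it through.** **1. The sections side by side**

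| Patient | 'Data management and statistical analysis' | 'Concomitant treatments and forbidden drugs' |
|---|---|---|
| At least one infusion, then a prohibited drug | In the safety set | Data not used |
| 10 days dosed with observations, prohibited drug during treatment | In the FAS; out of the PPS if the deviation is major | Data not used |
| 10 days dosed with observations, prohibited drug during follow-up | In the FAS, end-of-treatment grade already recorded | Data not used, including that grade |

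Each row gives two incompatible instructions. Only the PPS definition makes room for excluding deviators.

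**2. The plan's own sample size**

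Inputs from 'Sample size': control rate 0.8182, Guhong rate 0.9394, two-sided α = 0.05, β = 0.2, 1:1 allocation. The standard unpooled formula gives

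n = [0.9394 × 0.0606 + 0.8182 × 0.1818] × (1.960 + 0.842)² / (0.1212)² = (0.0569 + 0.1487) × 7.849 / 0.01469 = 109.9, so 110 per group.

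The pooled version gives 113. The stated 111 is reproduced within tolerance. Attrition: 111 / 0.85 = 130.6, against the stated 130. With all 130 per arm kept, the planned difference is 12.1 points and power (pooled test) is 85.4%.

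**3. Illustration of the deletion rule**

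Assumptions, none of them in the document: every deleted patient is a failure, and a share f of an arm's failures is deleted, with f from 25% to 50%. An arm with true effective rate p then shows

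p* = p / [p + (1 − p)(1 − f)].

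*Planned effect true (81.82% vs 93.94%)*

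| Failures deleted | Control p* | Guhong p* | Difference (points) | Power |
|---|---|---|---|---|
| None | 81.8% | 93.9% | 12.1 | 85% |
| 25% in both arms | 85.7% | 95.4% | 9.7 | 75% |
| 50% in both arms | 90.0% | 96.9% | 6.9 | 59% |
| 25% in control only | 85.7% | 93.9% | 8.2 | 59% |
| 50% in control only | 90.0% | 93.9% | 3.9 | 21% |
| 25% in Guhong only | 81.8% | 95.4% | 13.6 | 93% |
| 50% in Guhong only | 81.8% | 96.9% | 15.1 | 98% |

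For example, at f = 0.25 in control: 0.8182 / (0.8182 + 0.1818 × 0.75) = 0.8572.

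*No true effect (81.82% in both arms)*

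Equal deletion in both arms leaves a zero difference and type I error of 5%. Deletion in one arm only gives:

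- f = 25%: 85.7% vs 81.8%, a spurious 3.9 points. The affected arm keeps 130 × (1 − 0.25 × 0.1818) = 124.1 patients. The null standard error is 0.0463 and the actual one 0.0462. Upper-tail rejection is Φ[(0.0390 − 1.96 × 0.0463) / 0.0462] = 0.131; the other tail adds 0.002. Total: about 13%.
- f = 50%: 90.0% vs 81.8%, a spurious 8.2 points with 118.2 patients kept. Upper-tail rejection is Φ[(0.0818 − 1.96 × 0.0445) / 0.0437] = 0.451; the other tail is negligible. Total: about 45%.

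These deletions are 0.25 × 18.18% = 4.5% and 0.50 × 18.18% = 9.1% of the affected arm. Both lie inside the planned attrition of under 15%, so they would not look unusual.

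**The case against.** Four things can fairly be said for the plan.

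- **Who takes prohibited drugs.** The ban covers any medicine that could influence results, not only anti-anginal treatment, and conventional treatment continues in both arms. A reader might infer that users are treatment failures. The document does not say so, and a drug taken for an unrelated illness would carry no such information. This stands: the link to outcome is plausible, not established.
- **Which section governs.** A reader might infer that safety data will certainly be deleted. The concomitant-treatment section names no analysis set, and the set definitions carry no such exclusion, so the outcome is undetermined. What stands is the contradiction. It needs resolving because the discard rule is affirmative and unqualified.
- **Overlap with the FAS definition.** The FAS already requires 10 days of dosing, so a patient taken off before then drops out of it anyway. That is correct, and it limits what the discard rule adds to efficacy under the present FAS to patients who complete 10 days, including those who take a prohibited drug during follow-up. The safety conflict is unaffected.
- **Direction.** A reader might infer that the rule favours Guhong. The document gives no usage by arm. Equal deletion, or more deletion in control, works against Guhong when the planned effect is real; more deletion on Guhong works in its favour.

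The reference to the signed consent form does not settle the conflict, because the same article defines the safety set without this exclusion.

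**Conclusion.** The contradiction is explicit and needs no assumption: the article instructs both that prohibited-drug users' data go unused and that everyone treated at least once is evaluated for safety, and its FAS does not exclude these users either. Applied literally, the discard rule is a post-randomisation exclusion from efficacy and a removal of treated patients from safety.

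The size of any efficacy bias cannot be derived from the document. The ranges above rest on the assumptions that all deleted patients are failures, that 25% to 50% of failures are deleted, and that all 130 per arm would otherwise be analysed. They show that a modest loss of patients could matter, not that it will occur. Its direction is open.

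**What to change.** Reconcile the two sections on the use of data:

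1. Record prohibited-drug use as a protocol deviation, and exclude such patients from the PPS only.
2. Keep all data collected from them in the safety set and the FAS.
3. Still collect the day-10 assessment where consent allows.
4. Pre-specify how use before the day-10 assessment is handled in the FAS primary analysis. Either the observed day-10 grade is used or the patient is counted as having no effect, with the other as a sensitivity analysis. Both are defensible; the choice must be fixed in advance.
5. State that use after day 10 does not change the day-10 grade.
6. Check that the signed consent wording permits keeping the data. Enrolment is under way, so the check must cover patients who have already consented.

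This concerns data use only, not which drugs are prohibited or when treatment stops. The cost is a wording change, possibly a consent amendment, and a few more completed visits. Assessments not made at the time cannot be recovered later.

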### Efficacy assessment

#### Primary outcome

The criteria for therapeutic efficiency evaluation is based on the principles for clinical research reports on cardiovascular drugs formulated by the National Health and Pharmaceutical Bureau of China [13] by comparing the anginal attack frequency and ECG changes before and after treatment in the two groups of participants. Specific evaluation criteria are shown in Table 3.

**Table 3 Tab3:** Evaluation criteria on the therapeutic efficiency

Three-graded criteria	Detailed description	Classification
Significant improvement	Anginal attacks disappeared or significantly improved, decreased by 80%; electrocardiogram (ECG) returned to normal or substantially normal	Significantly effective
Improvement	Anginal attacks improved or the frequency of anginal attacks decreased by 50–80%; the descending ST segment of the ECG rose ≥ 0.05 mV, and the ascending ST segment fell ≥ 0.05 mV, but still did not return to normal; or the T wave of the main ECG lead changed from flat to upright; or the T wave changed from inverted to shallow by more than 50%	Effective
No improvement	No change or even aggravation of anginal attacks, no decrease or even increase of the frequency of angina pectoris attacks, no change or even aggravation of ECG ST-T segment	No effect

#### Secondary outcomes

Secondary outcomes include changes in TCM symptoms and signs scores (Table 4), the average frequency of angina pectoris, the ECG, the indicators of inflammation, endothelial function and myocardial metabolites.

**Table 4 Tab4:**
[figure not shown]
Symptom and sign scoring system

#### Change in scores of TCM symptoms and signs

The TCM syndromes scoring system used in the study follows the guidelines of clinical research on the treatment of coronary heart disease (chest pain) with new Chinese medicine [14], in which all symptom and sign scores are graded (Table 4). A total of nine kinds of symptoms include: chest pain, chest tightness, breathlessness, palpitations, mental fatigue, aversion to cold, and cold limbs, lumbar and knee soreness, spontaneous sweating, and insomnia. The score is 0 points for asymptomatic, 1 point for mild, 2 points for moderate and 3 points for severe. The total score ranges from 0 to 27. The lower the score, the milder the symptoms.

#### The average frequency of angina pectoris

The average frequency of angina pectoris from the first day of enrollment to the end of treatment and at 8 weeks of follow-up will be recorded in the CRF. Each participant will be instructed to record any change in their symptoms of angina pectoris in their patient diary daily.

#### Indicators of inflammation, endothelial function and myocardial metabolism

Indicators of inflammation, endothelial function and myocardial metabolism of participants before and after treatment will be tested in this study. Inflammatory indicators include hypersensitive c-reactive protein (hs-CRP), interleukin-6 (IL-6)、tumor necrosis factor-alpha (TNF-α). Endothelial function indices include nitric oxide (NO), endothelin-1 (ET-1)、and thromboxane A2 (TXA2). Myocardial metabolism indicators include cardiac troponin I (cTnI) and creatine kinase isoenzyme (CK-MB). Inflammatory reaction plays a significant role in the occurrence and development of the coronary heart disease symptom angina pectoris. TNF-α is the initiation factor of the inflammatory response, which stimulates the synthesis and release of pro-inflammatory response factors (IL-6 and CRP), leading to the aggravation of the inflammatory response and the formation of thrombus [15, 16]. NO and ET-1 are the two most important vasoactive factors and the sensitive indicator of endothelial dysfunction in the human body [17], NO can relax blood vessels [18], while ET-1 can promote vasoconstriction [19]. After vascular endothelial injury, TXA2 will promote platelet aggregation and vasoconstriction [20]. As for cTnI and CK-MB, they are ideal metabolites for early myocardial injury [21].

#### Safety evaluation

Liver and kidney function, routine blood tests, routine urine tests, routine fecal tests and an ECG before and after treatment will be used to assess for drug safety and adverse reactions.

#### Data management and statistical analysis

The Drug Clinical Research Center of Guangzhou University of TCM will be responsible for the data statistical analysis. Two independent data administrators are in charge of reading the CRFs and recording data on the EpiData 3.1 software. Clinical research assistants (CRA) and investigators will re-check and review the accuracy and consistency of the data. After entering and reviewing, the database will be locked and the statistical analysis will be performed only with the permission of the sponsor, the principal investigator and the investigators.

The full analysis set (FAS) is the primary analysis set, in which patients should be dosed with *Guhong* injection or placebo for 10 days with clinical observations recorded in the study. All subjects without any major protocol deviations will be included in the per-protocol set (PPS). Efficacy assessment will be performed through FAS and PPS. Safety evaluation will be conducted for those who have been treated at least once, which is defined as the safety set (SS).

All continuous data and normal distribution data are represented by mean ± standard deviation, with median and range for non-normal data. Classified data are expressed in frequency counts and percentages. Baseline balance between groups will be determined by a chi-square test or analysis of covariance (ANOVA). All the indicators of anginal attack frequency, inflammation, endothelial function and myocardial metabolites will be estimated and compared using the log-rank test. A Kaplan-Meier survival curve will be constructed, and the median time will be provided separately for each group with a two-sided 95% confidence interval. ANOVA and Bonferroni methods will be used to compare the TCM symptom and sign scores of the two groups. All collected data will be processed by professional statisticians using SAS 9.2 software; a two-sided *P* value of < 0.05 is considered statistically significant.

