### Withdrawal criteria

The withdrawal criteria include the following:
Experiencing serious complications or rapid deterioration of the condition during the trial, including anginal attack frequency increasing significantly, myocardial ischemia continuing to worsen, myocardial infarction, arrhythmia and other changesSerious adverse events occurring, which should lead to treatment being stopped according to the physician’s judgmentParticipants with important deviations in the implementation of the program, such as poor compliance and difficulty in evaluating drug effectsQuitting the clinical trial voluntarily

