### Emergency unblinding

If an emergency occurs, the patient group assignment should be unblinded and known to the drug administrators or dispensing nurses, and corresponding emergency measures will be taken. Researchers will report this special situation to the center’s principal within 24 h. At the same time, the cause of unblinding, the time of the emergency, the solution and the result must be filled in the case report form (CRF). Once the participant ‘s allocated intervention during the trials has been revealed, the case will be withdrawn and the data will be recorded on day 10 of the trial evaluation.

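### As written, the primary analysis set is a set of treatment completers, so patients who stop early because angina worsens leave the primary comparison

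*Protocol article*

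**What the plan says.** All references are to the protocol article.

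- **Data management and statistical analysis.** The FAS is named as the primary set for efficacy. Its members are to have received Guhong "injection or placebo for 10 days with clinical observations recorded in the study". The PPS is the subset without major protocol deviations. "Efficacy assessment will be performed through FAS and PPS". The safety set, defined in the same paragraph, needs only one treatment. No efficacy set of all randomised patients is named.
- **Interventions.** "The course of treatment is 10 days".
- **Withdrawal criteria.** Reasons include "anginal attack frequency increasing significantly", worsening ischaemia, infarction, arrhythmia, serious adverse events that stop treatment, poor compliance and the patient's own choice.
- **Emergency unblinding.** Once the allocation is revealed, "the case will be withdrawn and the data will be recorded on day 10 of the trial evaluation".
- **Concomitant treatments and forbidden drugs.** After use of a banned drug, "patients will be removed from the study and their data will not be used".
- **Primary outcome, Table 3.** The no-effect grade covers anginal attacks or ST-T findings that are unchanged or worse.

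**The concern.** Membership of the primary set depends on something that happens after randomisation, namely finishing the course. One route out of the course is deterioration of the condition that the primary outcome grades. Those patients would be failures under Table 3, but they leave both numerator and denominator. The effective rate then rises in each arm for a reason unrelated to benefit.

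If the loss of failures differs between arms, randomisation no longer protects the comparison. More failures lost on Guhong favours Guhong, and more failures lost on placebo works against it. Analysing the PPS alongside gives no protection, because the PPS can only remove further patients.

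This is a rule that the article states, not a detail left to a statistical analysis plan. A plan that follows it inherits the fault.

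**Working it through.** **Does the text define a completer set?** The FAS condition is 10 days of dosing, and the course is 10 days. The safety set uses at least one treatment, so the looser criterion was at hand and was not used for efficacy. On its natural reading the FAS is a completer set.

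**Who leaves it?**
- Worsening angina or ischaemia before day 10: out of the FAS, although a no-effect case under Table 3.
- Serious adverse event, arrhythmia or emergency unblinding: out of the FAS if dosing stops early. These are not Table 3 failures in themselves.
- Banned-drug use: data not used.
- Withdrawal after day 10, during the 8-week follow-up: stays in the FAS.

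**The plan's own figure.** The Sample size section gives 93.94% versus 81.82%, two-sided α = 0.05 and β = 0.2. The extracted formula does not show its squares, so the usual squared form is used:

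n = [0.9394×0.0606 + 0.8182×0.1818] × (1.960 + 0.842)² / 0.1212² = 0.2057 × 7.849 / 0.01469 = 109.9, or 110 per arm.

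The stated figure is 111, a match within rounding. 110/0.85 = 129.4, so 130 per arm. The plan therefore allows for losing up to about 0.15 × 130 = 19.5 patients per arm.

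**Possible bias with no true effect.** Assumptions (not in the documents): a rate r = 0.80 effective among all 130 randomised in each arm; a fraction w withdrawn before day 10; a share f of the withdrawn are failures.

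- Completer rate = [r − (1−f)w] / (1−w), among 130(1−w) patients.
- False-positive rate = Φ(d/SE − 1.96) + Φ(−d/SE − 1.96), where d is the difference in completer rates and SE is its unpooled standard error.

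| Withdrawn, arm A vs arm B | f | Completer rates, A vs B | d | SE | False positives |
|---|---|---|---|---|---|
| 5% vs 5% | 1 | 84.2% vs 84.2% | 0 | 0.046 | 5% |
| 5% vs 10% | 0.5 | 81.6% vs 83.3% | 0.0175 | 0.049 | 6.5% |
| 5% vs 10% | 1 | 84.2% vs 88.9% | 0.047 | 0.044 | 19% |
| 5% vs 15% | 0.5 | 81.6% vs 85.3% | 0.037 | 0.049 | 12% |
| 5% vs 15% | 1 | 84.2% vs 94.1% | 0.099 | 0.040 | 70% |

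Example, fourth row, arm B: (0.80 − 0.5×0.15)/0.85 = 0.725/0.85 = 0.853. Either arm may be Guhong. Swapping the arms reverses the sign of d and leaves the false-positive rate unchanged. With r = 0.8182 and a pooled test, the two f = 1 rows with unequal withdrawal give about 21% and 78%.

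**Power at 130 per arm once everyone is counted** (unpooled normal approximation). If the design rates already hold in all randomised patients, power is about 86%. If they hold only in completers and a fraction a of each arm withdraws and counts as failure, the rates become 0.9394(1−a) and 0.8182(1−a):

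| a | Rates | Power |
|---|---|---|
| 2% | 92.1% vs 80.2% | 80% |
| 5% | 89.2% vs 77.7% | 72% |
| 10% | 84.5% vs 73.6% | 59% |
| 15% | 79.8% vs 69.5% | 49% |

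**The case against.** The strongest defence is that the FAS sentence is loose wording in a condensed article: patients *should be* dosed for 10 days, which need not mean that anyone who was not is excluded. The Withdrawal criteria do not say that withdrawn patients' data are discarded, whereas the forbidden-drugs section does say so. For unblinded cases a day-10 record is expected. This stands as a reason not to claim that early stoppers cannot be in the FAS under any reading. It does not rescue the sentence, which on its plain meaning requires the full course, and nothing else in the article assigns these patients an outcome.

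Three stronger readings are tempting, and the documents do not support them:

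- *Every withdrawn patient is a treatment failure.* Only worsening angina or ischaemia meets Table 3. Adverse events, arrhythmia, unblinding, poor compliance and voluntary exit do not by themselves.
- *False positives of 19% or 70% are to be expected.* These need every withdrawal to be a failure and withdrawal two or three times as frequent in one arm. The 15% is the article's upper allowance for attrition of all kinds. At 15% of 130 with all failures, 19.5 of the 26 expected failures (20% of 130) would have to withdraw.
- *The bias favours Guhong.* The article gives no withdrawal rates by arm. Losing failures mainly on placebo would bias against Guhong.

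It is also fair to say that imputation of other missing outcomes belongs in the statistical analysis plan.

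**Conclusion.** The point holds. As the article defines it, the primary efficacy analysis is a completer analysis and not intention-to-treat, and it drops some patients who are failures by the trial's own criterion. Whenever withdrawals contain more failures than the arm as a whole, the effective rate is inflated. Type I error is at risk only if outcome-related withdrawal differs between arms.

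The size cannot be fixed from the documents. Under the stated assumptions the false-positive rate runs from its nominal 5% with equal withdrawal, through 6.5% to 19% for 5% versus 10%, to 12% to 70% for 5% versus 15%. In the extreme case the spurious difference is 9.9 points, against a planned effect of 93.94 − 81.82 = 12.12 points. The definition must be corrected because it decides who is counted in the primary comparison, whatever the true withdrawal pattern turns out to be.

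**What to change.** Change the analysis-set paragraph, before any results by arm are seen:

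1. Define the FAS as all randomised patients who received at least one infusion, analysed in the arm to which they were randomised.
2. Count patients withdrawn for worsening angina or ischaemia as no effect on the primary outcome.
3. Keep patients withdrawn after emergency unblinding in the FAS and use the day-10 data where recorded. Keep banned-drug users in the FAS as well, and reconcile this with the sentence that discards their data.
4. Add a sensitivity analysis that counts every missing primary outcome as failure.
5. Make 10-day completion a condition of the PPS only.

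Handling of other missing outcomes can stay with the statistical analysis plan.

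**Cost.** The edit itself is small, but it needs the reason and date of each withdrawal to be recorded. The forbidden-drugs section ties the discarding of data to the signed consent form, so the consent wording must be checked before those data are used. Power may fall: it stays at about 86% if 93.94% and 81.82% already describe all randomised patients, but is about 80%, 72%, 59% or 49% if they describe completers only and 2%, 5%, 10% or 15% withdraw and count as failures. The sample-size section should say which population its rates refer to and restate the power accordingly.

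### Log-rank test, Kaplan-Meier curve and median time are prescribed for attack frequency and eight biomarkers, none of which is a time-to-event variable

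*Protocol article*

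**What the plan says.** The section on data management and statistical analysis assigns one test to four groups of outcomes: "All the indicators of anginal attack frequency, inflammation, endothelial function and myocardial metabolites will be estimated and compared using the log-rank test". The next sentence adds the summary that goes with it: "A Kaplan-Meier survival curve will be constructed, and the median time will be provided separately for each group with a two-sided 95% confidence interval". Test, curve and summary are all survival methods, so this is not a slip of a single word.

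The outcome sections describe variables of another kind.

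- **Biomarkers.** "Indicators of inflammation, endothelial function and myocardial metabolism of participants before and after treatment will be tested in this study". The list has three inflammatory markers (hs-CRP, IL-6, TNF-α), three endothelial markers (NO, ET-1, TXA2) and two myocardial markers (cTnI, CK-MB). The Interventions section places these laboratory tests at the same two visits as the clinical assessment: "On the day of enrollment and at the end of treatment, the clinical symptoms and signs of angina pectoris will be recorded".
- **Angina.** The outcome is "The average frequency of angina pectoris from the first day of enrollment to the end of treatment", with a further value at 8 weeks of follow-up. The source is a diary: "Each participant will be instructed to record any change in their symptoms of angina pectoris in their patient diary daily".

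The Secondary outcomes section lists all of them as secondary: "the average frequency of angina pectoris, the ECG, the indicators of inflammation, endothelial function and myocardial metabolites" (the ECG, named in the same list, is not part of this point).

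**The concern.** A log-rank test compares the times at which a defined event occurs, allowing for patients whose event has not yet been seen. It needs an event, a time origin and a censoring rule. The article gives none of these for a laboratory concentration or for an attack frequency. The analysis section also says elsewhere that continuous data are summarised by mean and standard deviation, or by median and range, which does not fit a median time with a confidence interval.

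The trial's mechanistic aim, set out in the Background and Discussion, is to explain the drug's action through inflammation and endothelial function. That aim rests on these biomarkers. As written, they have no between-group analysis that can be carried out meaningfully, and no effect estimate (difference, ratio or rate ratio). An analyst would have to substitute another method, and if that happens after data are seen, the choice is open to the results.

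**Working it through.** **1. The plan's own figure.** The only calculated figure in the plan is the sample size, which rests on the binary effective rate. With the squared difference in the denominator:

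n = [0.9394 × 0.0606 + 0.8182 × 0.1818] × (1.960 + 0.842)² / 0.1212² = 109.9, so 110 per group against 111 stated.

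It reproduces to within one patient and does not involve the log-rank test.

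**2. Outcomes against requirements.**

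| Outcome | What is recorded | Event | Time origin | Censoring rule |
|---|---|---|---|---|
| 3 inflammatory markers | value before and after treatment | none | none | none |
| 3 endothelial markers | value before and after treatment | none | none | none |
| 2 myocardial markers | value before and after treatment | none | none | none |
| Attack frequency | average over a period, from a diary | none | none | none |

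That makes 3 + 3 + 2 + 1 = 9 outcomes.

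**3. Reading A: the day of measurement is the time.** All 260 patients have day 10 as planned, counted as an event. With one common time, N = d = 260 and 130 per group:

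- expected events in one group = 260 × 130/260 = 130, equal to the observed 130, so the numerator is 0;
- variance = d × (n₁/N) × (n₂/N) × (N − d)/(N − 1) = 260 × 0.5 × 0.5 × 0/259 = 0.

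The statistic is 0/0. Running it in software failed with a singular variance matrix. There is no test.

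**4. Reading B: the concentration is entered as if it were a time, uncensored.** The log-rank test then becomes a rank test with exponential (Savage) scores on the post-treatment values. Its asymptotic efficiency relative to the t-test for a shift in normal data is

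[∫₀¹ (−ln(1 − u) − 1) Φ⁻¹(u) du]² = 0.9032² = 0.816.

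A simulation (130 per group, shift of 0.35 SD, 2,000 runs) agrees in direction: power was 0.742 for the log-rank test on the values and 0.8195 for the t-test.

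ANCOVA on baseline reduces the residual variance by the factor 1 − ρ², where ρ is the baseline-to-post correlation. The article gives no ρ, so two values are assumed:

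- ρ = 0.5: 0.816 × 0.75 = 0.61;
- ρ = 0.7: 0.816 × 0.51 = 0.42.

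Only the 0.816 comes from the choice of test. The rest is the cost of ignoring baseline, which an unadjusted t-test would also pay.

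**5. Reading C: a time derived from the diary.** Time to first attack, or to an attack-free state, could be built from daily entries. The article defines neither, and no such variable could serve the eight biomarkers.

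**The case against.** The strongest objections concern scope.

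- **Reading B is not invalid in the strict sense.** In a simulation with log-normal values and 111 per group (10,000 runs), its type I error was 0.051. That stands. But the article does not describe this procedure, its median would still not be a time, and it would give no usable effect estimate. The efficiency figures apply to this reading only.
- **The diary could support a survival analysis of attacks, and the article may have compressed one into a single sentence with the biomarkers.** This is possible for attack frequency and stands to the extent that defining an event would be an acceptable repair there. It does not cure the text, which states the outcome as an average frequency, and it does nothing for the biomarkers.
- **Only secondary outcomes are affected.** Correct. The primary graded efficacy outcome also draws on attack frequency, but through percentage reduction and not through this test. Attack frequency should therefore not be called the trial's main symptom outcome.
- **An analysis plan not shown may correct this.** The point is not about missing detail. The article names a method that does not fit its own outcomes. A plan that follows it inherits the error, and one that departs from it contradicts the published protocol.

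**Conclusion.** The concern holds: the method is wrong as written for nine secondary outcomes, and certainly so for the eight biomarkers. On the measurement-day reading there is no test. On the values-as-times reading there is a test without an interpretable median time, with efficiency of about 0.82 against a t-test. Against ANCOVA it is 0.61 to 0.42 under assumed correlations of 0.5 to 0.7. Those figures assume normal data and uncensored values and are illustrative; the conclusion rests on the type of variable and does not need them. The primary comparison and the sample size stand. The correction must be made, because the prescribed analysis cannot be carried out meaningfully and the repair costs very little.

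**What to change.** Delete both the log-rank sentence and the Kaplan-Meier sentence and replace them as follows.

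- **Biomarkers.** ANCOVA of the log-transformed end-of-treatment value on treatment, log baseline and centre, reported as a geometric mean ratio with 95% confidence interval. If many cTnI or CK-MB values fall below the detection limit, use a rank test or compare the proportions above the limit. Write the model out, because the article currently abbreviates analysis of covariance as ANOVA.
- **Attack frequency.** A negative binomial model of the attack count, with log diary-days as offset and baseline frequency as covariate, reported as a rate ratio with 95% confidence interval, separately for the treatment period and the 8-week follow-up. Rank ANCOVA is an acceptable alternative.
- **Survival methods.** Keep log-rank and Kaplan-Meier only if a true time-to-event variable is added, with its event, time origin and censoring rule.

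Other baseline-adjusted or count models would also serve; what matters is that one is named for each outcome.

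The cost is wording only. Biomarker baselines are already collected. The primary outcome compares attacks before and after treatment, so a pre-treatment attack frequency is already required, but its recording window is not stated in the text and should be defined. Make the change before anyone sees unblinded data, including at the planned interim analysis.
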